##### Feasibility and acceptability

Feasibility and acceptability of the implementation strategy among staff in the 2 intervention sites will be measured by two 4-item validated measures: the Acceptability of Intervention Measure (AIM), and Feasibility of Intervention Measure (FIM) (e.g., the implementation strategy seems easy to use; the implementation strategy meets my approval) [67]. We will also adapt these measures to assess patients’ views on feasibility and acceptability of the text-messaging intervention to provide context to the effectiveness/reach outcomes.

##### Qualitative measures

Semi-structured interview guides for staff will be developed using concepts from the Organizational Readiness to Change Assessment, an instrument designed to assess the core elements of the i-PARIHS model, as well the aim 1 interview guide (e.g., What was it like to offer the text interventions to patients?) [91]. Semi-structured interview guides for patients will be adapted from a previous text-messaging study [92] in order to provide context to the reach/effectiveness data (e.g., Describe how the intervention was offered to you? What was it like for you to receive messages? What aspects of the text messaging, if any, do you think helped/did not help? What made you interested in enrolling in the text-messaging program?).

#### Data collection procedures

##### Patients

A random sample (*n* = 250) of adult patients who screen positive for UAU and enroll in the text intervention will be invited via text message to participate in a survey on the intervention’s feasibility and acceptability 1 month after enrolling in the intervention. A link will be sent to participants via the text-messaging platform for them to participate in the online survey, review informed consent study information sheet, and receive a $15 e-gift card for their participation.

We will also invite 10 patients to participate in qualitative interviews from each of the 4 EDs with a question at the end of the survey inquiring if they are interested; we will then follow up by phone to schedule. A verbal consenting procedure will be conducted by the interviewer along with an information sheet provided to the patient.

##### Staff

Clinical staff members at the 2 intervention EDs will be invited by email to participate in an online survey; during month 6 of the trial, they will receive a study information sheet informing them of their rights as a research participant. One chairperson per site will also be interviewed with the semi-structured interview guide. We will ask chairpersons to identify 20 staff per intervention ED (*n* = 40) to participate in semi-structured interviews, targeting those with knowledge of the intervention implementation. Staff and patients will have the option to complete the interview in-person or over the phone; interviews will be recorded. Staff will receive a study information sheet and a verbal consenting procedure will be used. Additional interviews will be conducted if our sample does not reach saturation [77].

#### Analysis

The same procedures described in aim 1 will be used to analyze qualitative data for aim 3. For the reach/effectiveness quantitative data, we will calculate a proportion for each study condition (e.g., numerator: # of patients in control or intervention sites who enrolled in the intervention; denominator: # of patients with positive AUDIT-C) and use *z*-tests for independent proportions [93] to examine whether control and intervention sites differ significantly. We will also use *z*-tests to examine differences in demographics between those eligible and enrolled to determine whether there are gender or racial disparities. For these proportional analyses [94], to achieve 80% power, a sample size of at least 300 in each condition is needed (total of 600) to detect a 10% difference in proportions with significance level of *p* = .05. For the feasibility/acceptability staff and patient survey data, we will calculate descriptive statistics for each. We will triangulate this quantitative data with the qualitative data by merging the results. No identifying information will be maintained by the study team for any staff or patients; all participants will be identified with a participant ID.

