### Aim 3: Examine the feasibility, acceptability, and preliminary effectiveness of the implementation strategy

#### Design

In line with recommendations pertaining to the scope and target outcomes of pilot studies for implementation trials [83–85], the main goal of this pilot trial is to assess the (1) feasibility (i.e., perceptions among ED clinical staff members that the implementation strategy can be successfully used), (2) acceptability (i.e., perceptions among ED clinical staff members that the implementation strategy is agreeable, palatable, or satisfactory), and (3) and preliminary effectiveness of the implementation strategy. We will operationalize our effectiveness outcome as “reach” (i.e., proportion of eligible patients that enroll in the text intervention), which is a key outcome recommended in the implementation science literature [83, 85–87]. The design is a mixed method, two-armed, study in 4 EDs (2 assigned to the new implementation strategy vs. 2 implementation as usual control). Qualitative and quantitative measures will be collected and analyzed simultaneously and merged—qualitative data will provide context to and explanation of the quantitative results in a complimentary way, representing a QUAL + QUAN structure that gives equal emphasis to both types of data [65].

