#### Study site randomization

The study will be conducted within a large integrated health system in the Northeast of the USA. Because the number of study sites for this pilot is relatively small, simple unrestricted randomization may not be sufficient to ensure balance between study conditions. Pairing of EDs would improve balance but may reduce study power and is not recommended for small numbers of clusters [88]. Therefore, we will use a minimization procedure to ensure overall balance on three important covariates: annual ED census, location (urban/suburban), and AUDIT-C positive rate. A computerized algorithm will be used to identify all possible allocations that meet the balancing constraints and one of the allocations will be randomly selected [89]. A data analyst not associated with the study will conduct this procedure to minimize bias. Study sites and data analysts will be blinded to the study condition.

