#### Data sources and measures

##### Effectiveness/reach

Effectiveness will be examined by calculating how many patients were eligible (positive AUDIT-C) based on EHR data and the proportion who enrolled in the intervention as collected by the text platform. Demographics will also be collected from the EHR and text platform to examine differences in characteristics between who was eligible based on AUDIT-C score and who enrolled. In the text platform, each study site will have a unique enrollment text code number, allowing for tracking of patients that enrolled by site and when they enrolled, demographics, and responses to the intervention tailoring questions (e.g., drinking patterns, self-efficacy, motivation). We anticipate there will be ~5000 UAU eligible patients identified during the study trial period based on (1) sites’ current census, (2) current screen positive rates, and (3) screening completion rates based on our previous evaluations in this integrated health system.

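### Reach is compared as one volume-weighted proportion per arm, ignoring the ED as unit of allocation and the location factor, so a chance difference in urban/suburban mix can distort the realised contrast

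*Protocol article*

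**What the plan says.** All references are to the protocol article, Methods, Aim 3.

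- **Design.** Four EDs are randomised: "2 assigned to the new implementation strategy vs. 2 implementation as usual control".
- **Study site randomization.** A constrained allocation is used "to ensure overall balance on three important covariates: annual ED census, location (urban/suburban), and AUDIT-C positive rate". An algorithm is to "identify all possible allocations that meet the balancing constraints and one of the allocations will be randomly selected".
- **Effectiveness/reach.** About 5,000 eligible patients are expected, a figure built from census, screen-positive rate and screening completion. Each site has its own enrolment code, so enrolment can be counted by ED.
- **Analysis.** "we will calculate a proportion for each study condition", with a numerator counting the number "of patients in control or intervention sites who enrolled in the intervention" and a denominator of patients with a positive AUDIT-C. The comparison uses z-tests "for independent proportions [93] to examine whether control and intervention sites differ significantly". The planning statement is that "to achieve 80% power, a sample size of at least 300 in each condition is needed (total of 600" patients, for a 10% difference at the .05 level.

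The Analysis section does not use site, location, census or AUDIT-C positive rate in the reach comparison.

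**The concern.** Summing patients over an arm's two EDs gives the larger ED the larger say. Balancing EDs on location and on total census does not equalise the urban share of eligible patients in the two arms. Where that share differs and urban and suburban EDs have different reach, the pooled difference mixes the effect of the strategy with the mix of EDs.

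The reach difference is the trial's effectiveness result. Under the Discussion section it also enters, together with feasibility and acceptability, the decision on a full-scale trial. A few points of artefact, tested as though patients were independent, could make the strategy look better or worse than it is in the one allocation that is actually run.

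**Working it through.** **1. The plan's own figure.** Control reach is not stated, so it was scanned. With the pooled-variance formula, two-sided 0.05 and 80% power, 20% vs 30% gives

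n = (1.96·√(2·0.25·0.75) + 0.842·√(0.20·0.80 + 0.30·0.70))² / 0.10² ≈ 294 per arm,

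and 21% vs 31% gives 301. So 300 per condition reproduces for a control reach near 20%, reading 10% as 10 points, with no design effect. At 30% vs 40% the result would be 356. Patients are treated as independent.

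**2. Can balanced EDs leave an unequal patient mix?** Yes. Assume urban EDs with census 60k and 40k, suburban EDs with 60k and 40k, and equal positive and screening rates. Of the six possible allocations:

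- two put both urban EDs in one arm (unbalanced on location);
- two give 60U+60S vs 40U+40S (equal shares, but totals of 120k vs 80k);
- two give 60U+40S vs 40U+60S (totals of 100k each, urban share 60% vs 40%).

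Only the last pair balances both location and census, and both of its members have the unequal mix. In addition, screening completion helps determine eligible volume but is not a balancing factor.

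**3. Size of the artefact.** Inputs: 2,500 eligible per arm (half of about 5,000, an assumption), one urban and one suburban ED per arm, and no strategy effect. Then

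pooled difference = (urban share, intervention − urban share, control) × (urban reach − suburban reach).

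| Urban share, intervention / control | 5-point gap (25% vs 20%) | 10-point gap (30% vs 20%) | Planned z, 10-point gap |
|---|---|---|---|
| 50 / 50 | 0 | 0 | 0 |
| 55 / 45 | 0.5 | 1 | 0.82 |
| 60 / 40 | 1 | 2 | 1.63 |
| 70 / 30 | 2 | 4 | 3.27 |
| 80 / 20 | 3 | 6 | 4.90 |

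A 20-point gap doubles the 10-point column. In every row the within-location contrasts are zero, and so is the difference in unweighted ED means. Swapping the arms reverses the sign, so the average over the two mirror allocations is zero.

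**4. Relation to clustering.** Take the 70/30 row. The intervention arm has 1,750 urban at 30% and 750 suburban at 20% (27% pooled); the control arm has 750 and 1,750 (23%). The planned SE is √(0.25·0.75·2/2500) = 0.01225, so z = 0.04/0.01225 = 3.27. With the ED as unit, each ED's residual is ±52.5 enrolments (for example 525 − 1,750·0.27). Variance per arm = 2·(52.5² + 52.5²)/2500² = 0.00176, SE of the difference = √0.00353 = 0.059, and z = 0.67. This SE is rough with two EDs per arm, but the apparent significance comes from treating patients as independent.

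More generally, with 1,250 patients per ED the design effect is 1 + 1,249·ICC. The planned test's type I error, 2·(1 − Φ(1.96/√DE)), is about 0.19 at ICC 0.001, 0.47 at 0.005 and 0.59 at 0.01. The document gives no ICC; these values are assumed.

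**5. What remains testable.** Four EDs in two arms leave 2 df (critical t 4.30). Adjusting for location leaves 1 df (12.71).

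**The case against.** - **A reader might infer systematic bias.** The documents do not support that. The allocation is drawn at random among acceptable ones, each with an equally acceptable mirror, and the artefact cancels over the pair (taking eligible volumes not to depend on arm). This objection stands. What is left is chance confounding in the allocation actually drawn, and averaging over an allocation that was not drawn does not correct the reported estimate.
- **A reader might infer a defect separate from clustering, one that a corrected standard error would not touch.** That also goes too far. Differences in reach between EDs are between-cluster variation, and an ED-based standard error reflects them (step 4). The point estimate would still carry the artefact, but it would no longer look precise.
- **The size rests on undocumented inputs.** This stands. No section says that reach differs by location, that the mix will differ, or that there are two EDs of each type. Constraining census and positive rate also limits the imbalance.
- **The remedy resembles a paired analysis, and the randomisation section declined to pair EDs because of power and the small number of clusters.** This stands as a limit on testing. It does not argue against a location-balanced point estimate reported descriptively.
- **Equal ED weights depart from the definition of reach as a proportion of patients.** True, and a cost to be stated.
- **The article says "Demographics will also be collected from the EHR and text platform", so one might propose standardising on demographics too.** That would not address location mix, and it needs joint strata with matching categories that the article does not promise.

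**Conclusion.** The point holds in a limited form. The Analysis section fixes a volume-weighted comparison that ignores both the unit of allocation and the location factor on which the EDs are balanced. If reach differs by location and the urban share of eligible patients differs between arms, the realised difference is confounded by chance with location. The artefact is 1 to 6 points for an assumed 10-point gap, 0.5 to 3 for a 5-point gap, and zero for an equal mix, against the 10-point planning difference. The gap, the mix and the even split of patients between arms are assumptions.

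The larger weakness at the same place is the independent-patient z-test; the location artefact is one component of the between-ED variation that this test leaves out. For a four-ED pilot with progression criteria still to be set, this is a modest but inexpensive correction.

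**What to change.** In the Aim 3 Analysis section:

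1. Report reach (enrolled / eligible) for each of the four EDs.
2. If each arm has one urban and one suburban ED, make the main point estimate the average of the two within-location contrasts: ½·[(urban intervention − urban control) + (suburban intervention − suburban control)]. Otherwise, use the difference between arms in the unweighted mean of the two ED proportions.
3. Keep the pooled proportion per condition as description only.
4. Do not rest significance on the patient-level z-test; present the contrast as descriptive.

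**Cost.** A few lines of wording and no new data, since enrolment is already tracked by site. The estimate gives each ED equal weight, not each patient. If sampling error were the only source of variance, the variance of an arm's mean relative to pooling would be ¼(1/n₁ + 1/n₂) ÷ (1/2,500). That is 1.04 for EDs of 1,500 and 1,000, 1.19 for 1,750 and 750, and 1.56 for 2,000 and 500. Where between-ED variation dominates, little or no precision is lost. Any location-adjusted test has only 1 df, and the text should say so.

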Aim 2: use a stakeholder-engaged intervention mapping process to develop a multi-component implementation strategy for EDs

Aim 3: conduct a mixed method 2-arm cluster randomized pilot study in 4 EDs that serve ~11,000 UAU patients per year to assess the feasibility, acceptability, and preliminary effectiveness of the implementation strategy

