## Discussion

EDs are under pressure to provide services for UAU and are potentially significant points of intervention for UAU. Text-messaging interventions have the potential to be a scalable solution that could be used by almost any ED patient and may better support underserved populations. However, little is understood about how to ensure that ED staff systematically offer these products to patients nor how to best engage patients with them during an ED visit. This study will develop and test a comprehensive set of implementation strategies for text-messaging alcohol interventions under “real world” conditions. We will use a deliberative stakeholder-guided intervention mapping procedure to develop the implementation strategy. While applied widely to development of public health interventions, this intervention mapping approach is less frequently used to develop implementation strategies but offers great potential to align the selected implementation strategies and terminology in the implementation science literature, making the strategy more easily replicable for others wishing to use the approach.

In terms of future implications of study findings, as recommended in Pearson et al. [83], the research team and stakeholder group will set a priori criteria to determine whether to progress to a larger scale, fully powered hybrid implementation-effectiveness trial based on preliminary implementation strategy effectiveness in conjunction with feasibility and acceptability [94, 95]. Trial results will be shared with the stakeholder group as well as at scientific conferences and in scientific publications. This larger scale test, if warranted, would expand the number of EDs and the range of implementation outcomes beyond “reach” as well as examine cost-effectiveness of the implementation strategy and effectiveness of the text-messaging intervention in reducing patient alcohol use.

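### Reach is compared with a patient-level z-test, sized at 300 patients per condition, although whole EDs (2 per arm) are randomised; the nominal 5% level and 80% power are not delivered

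*Protocol article*

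**What the plan says.** The aims (end of Background) describe Aim 3 as a "2-arm cluster randomized pilot study in 4 EDs that serve ~11,000 UAU patients per year". Aim 3, Design, gives the split: "study in 4 EDs (2 assigned to the new implementation strategy vs. 2 implementation as usual control". Under Study site randomization, whole sites are allocated: "we will use a minimization procedure to ensure overall balance on three important covariates", with one allocation drawn at random from those that satisfy the constraints.

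The effectiveness outcome is reach, the share of AUDIT-C-positive patients who enrol in the text intervention. For this outcome Aim 3, Analysis, states "we will calculate a proportion for each study condition" and then z-type "tests for independent proportions [93] to examine whether control and intervention sites differ significantly". The same paragraph states the size: "to achieve 80% power, a sample size of at least 300 in each condition is needed (total of 600", for a 10% difference at a significance level of .05. Data sources and measures, Effectiveness/reach, expects about 5,000 eligible patients in the trial period.

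The article contains no ICC, design effect, site term or cluster-level summary.

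**The concern.** The strategy is assigned to an ED and acts through its staff and workflow, so patients of one ED share both the allocation and whatever else makes that ED good or bad at enrolling patients. The article itself expects EDs to differ: the Aim 1 quantitative section lists staff hesitancy, lack of time and missing record prompts as factors that could limit an ED's ability to offer the intervention, and the randomisation section restricts allocation because so few sites may not balance by chance.

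A z-test for independent proportions carries only binomial patient-level variance. With two EDs per arm, between-ED variation does not average out, and adding patients within the same four EDs makes the mismatch worse. At stake are a significance statement that does not have its stated error rate, a power statement with the same defect, and the loss of the between-ED variance, which a larger cluster trial would need for planning. The Discussion says that progression will be judged "based on preliminary implementation strategy effectiveness in conjunction with feasibility and acceptability", so the reach result is one of the inputs to that decision.

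**Working it through.** **Inputs from the article.** 4 EDs, 2 per arm; at least 300 patients per condition; 10-point difference; 80% power; alpha .05; about 5,000 eligible patients.

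**Assumptions.** Two-sided test (sidedness is not stated). Equal EDs, so 5,000/4 = 1,250 per ED as expected and 600/4 = 150 per ED at the stated minimum. ICC from 0.001 to 0.05 (none is stated). Control reach is not stated; 20% is used where a value is needed.

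**1. The plan's own figure.** For individually randomised patients, n per arm = [1.96·sqrt(2·p̄·(1−p̄)) + 0.8416·sqrt(p1(1−p1) + p2(1−p2))]² / d². For 20% vs 30%: [1.96·sqrt(0.375) + 0.8416·sqrt(0.37)]² / 0.01 = (1.2002 + 0.5119)² / 0.01 ≈ 293.2, so 294 (313 with continuity correction). Power at 300 is 80.9%. The 300 is therefore reproduced as a calculation for independent patients, without a design effect. It also depends on the unstated control reach: 10% vs 20% needs 199, 30% vs 40% needs 356, and 44% vs 54% needs 392.

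**2. True type I error of the z-test.** Design effect DE = 1 + (m − 1)·ICC. True size = 2·[1 − Φ(1.96/sqrt(DE))].

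| ICC | DE, m = 1,250 | True size | DE, m = 150 | True size |
|---|---|---|---|---|
| 0.001 | 2.25 | 19% | 1.15 | 7% |
| 0.002 | 3.50 | 30% | 1.30 | 9% |
| 0.005 | 7.25 | 47% | 1.75 | 14% |
| 0.01 | 13.49 | 59% | 2.49 | 21% |
| 0.02 | 25.98 | 70% | 3.98 | 33% |
| 0.05 | 63.45 | 81% | 8.45 | 50% |

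Beta-binomial simulation (100,000 runs per setting; reach 10%, 20% and 44%; ICC 0.001, 0.005, 0.01, 0.02 and 0.05) agreed to within about 1 percentage point. The size reaches 50% at ICC of about 0.006 with 1,250 per ED and about 0.05 with 150 per ED. At 20% reach, ICC 0.006 is a between-ED standard deviation of sqrt(0.16·0.006) = 0.031, or 3.1 points.

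**3. Precision at 20% reach, ICC 0.01, 1,250 per ED.**
- Pooled: 1.96·sqrt(2·0.16/2,500) = 0.022, so ±2.2 points.
- ED-level: variance of one ED proportion = 0.16·13.49/1,250 = 0.00173. The difference of two means of two EDs has the same variance, so SE = 0.0416. With t on 2 df, 4.303·0.0416 = 0.179, so about ±18 points.

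**4. Power of a test that holds 5%.** The t-test on ED proportions (2 df) kept 4.9% to 5.2% in the simulation. Its power for 20% vs 30%:

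| ICC | 1,250 per ED | 150 per ED |
|---|---|---|
| 0.001 | 78% | 33% |
| 0.005 | 40% | 24% |
| 0.01 | 26% | 19% |
| 0.02 | 16% | 14% |
| 0.05 | 10% | 9% |

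**5. Randomisation test.** There are at most C(4,2) = 6 allocations, so the smallest two-sided p is 2/6 = 0.33. The balancing constraints can only reduce the number. If, for example, two EDs were urban and two suburban and location had to balance, 4 would remain and the floor would be 2/4 = 0.50.

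**The case against.** The best defence is that this is a pilot. Effectiveness is called preliminary, a fully powered trial is to follow, and the progression criteria have yet to be set by the team and stakeholders. That limits the consequences, but it does not rescue the method: the Analysis section fixes a named test, its purpose and its sample size, so this is not a detail left to an analysis plan.

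A second defence is that the inflation depends on quantities the article does not give. This stands, and it rules out several stronger statements that a reader might infer:

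- *That a significant result would be false about half the time or more.* The rate is 19% to 30% at ICC 0.001 to 0.002 with the expected numbers, and at 600 patients it reaches half only near ICC 0.05. These are also error rates when the strategy has no effect, not the share of significant results that are false. Constrained allocation may lower them somewhat; unequal EDs would raise them.
- *That any ordinary difference between EDs would come out significant.* At 20% reach, a difference between arms of less than about 2.2 points would not.
- *That four EDs permit no valid p-value.* The floor of 0.33 or more applies to randomisation tests. A 2-df t-test on ED proportions is valid under its model, but weak.
- *That a p-value will decide progression.* The Discussion names preliminary effectiveness alongside feasibility and acceptability, and no p-value rule.

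Keeping an ED-level test, or labelling the comparison as descriptive, would also remove the error. Preferring estimation is a judgement based on the low power.

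**Conclusion.** The point holds in this form: the between-arm reach test and its sample size treat patients as independent when EDs are randomised, and nothing elsewhere in the article corrects this. The nominal 5% level is not held at any non-zero ICC examined. With about 1,250 patients per ED, even ICC 0.001 nearly quadruples it. The 80% power at 300 per condition applies only without clustering, and roughly at a control reach of 20% if the test is two-sided. The exact size of the inflation is not known, because it rests on an assumed ICC and equal ED sizes. The mismatch between design and test rests on neither.

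**What to change.** Replace the pooled z-test between conditions with an ED-level analysis:

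- report reach for each of the 4 EDs;
- report the arm means of the ED proportions and their difference, with a 95% CI from the ED-level summaries (t, 2 df), presented as preliminary estimation;
- report the between-ED variance or ICC, with its imprecision acknowledged, for planning the larger trial.

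Restate the sentence on 300 per condition and 80% power as applying only without clustering, and give the control proportion behind it, or remove it.

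The cost is in the analysis text only. Site-specific enrolment codes already allow reach to be computed by ED, so no site, data item or procedure changes. The downside is a much wider interval (about ±18 instead of ±2.2 points at 20% reach and ICC 0.01) and low power if an ED-level test is kept. A randomisation test is no way round this, since its two-sided p cannot fall below 0.33 at best.

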The focus of this study is primarily on studying implementation outcomes, and not patient outcomes; therefore, we will not randomize patients to the text-messaging intervention; instead, all patients will receive the intervention. However, we will collect valuable data from patients to assess feasibility and acceptability of the intervention from their perspective; determine the proportion who engage with the intervention in a real-world situation; examine disparities in gender, race, and ethnicity in enrolled vs. not; and understand why patients enrolled. All of the more than 150 hospitals in New York State are now required by state regulation to screen for substance misuse and such policies are being implemented elsewhere [96]; therefore, findings have the potential to be applied state- and nation-wide and a large number of sites would be available for a larger study.

This project moves forward the implementation science on technology interventions, a fairly new area of research. While the technology focus of this project is on text messaging, findings may be broadly applicable to patient-facing mHealth technologies. Text-messaging interventions have the potential to reach as many patients impacted by UAU as possible, including those traditionally underserved, in a scalable, low-burden manner; this study will illuminate strategies to reach that potential.

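### The disparity test sets the enrolled against the eligible group that contains them, so an independent-samples z-test is too conservative; the Discussion describes the valid contrast.

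*Protocol article*

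**What the plan says.** Three places in the Protocol article describe the disparity analysis.

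- **Aim 3, Analysis:** z-tests are planned, described as "tests to examine differences in demographics between those eligible and enrolled to determine whether there are gender or racial disparities". The sentence before it names the arm comparison as z-"tests for independent proportions [93] to examine whether control and intervention sites differ significantly". No other kind of z-test is named.
- **Aim 3, Effectiveness/reach:** demographics are taken from the electronic health record (EHR) and the text platform "to examine differences in characteristics between who was eligible based on AUDIT-C score and who enrolled".
- **Discussion:** the study will "examine disparities in gender, race, and ethnicity in enrolled vs. not".

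The Aim 3 Design section defines reach as the "proportion of eligible patients that enroll in the text intervention". The enrolled are therefore a subset of the eligible. The Effectiveness/reach section expects about 5,000 eligible patients and gives each site its own enrollment code. No section says whether the disparity analysis is done overall, by arm or by ED.

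**The concern.** A test for independent proportions assumes that no patient is counted in both samples. Here every enrolled patient is counted twice, once as enrolled and once as eligible. The two proportions are positively correlated, and the test ignores this. Its standard error is too large, and more so as reach rises. The analysis could then report no gender or racial disparity when one exists. That matters because the article presents reaching underserved patients as a main attraction of text messaging and lists disparities among what the study will examine. The Discussion also states a different contrast from the two Methods sections, so the article does not fix which comparison will be made.

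**Working it through.** **The plan's own figure.** The Analysis section asks for 300 per condition to detect 10 points with 80% power at 0.05. The base rate is not stated. With 20% vs 30%, two-sided, n = [1.96·√(2·0.25·0.75) + 0.842·√(0.16 + 0.21)]² / 0.10² ≈ 294 per arm, and power at 300 is 80.9%. The figure is reproducible under that assumption and is not in dispute.

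**Variance.** Let N be the number eligible, n = fN the number enrolled, and p the share of a demographic group. The eligible are the enrolled plus the not enrolled, so

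p_enrolled − p_eligible = (1 − f)(p_enrolled − p_not).

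Under no disparity, the variance of the right-hand side is (1 − f)²·p(1 − p)·[1/(fN) + 1/((1 − f)N)] = p(1 − p)(1/n − 1/N). The independent-samples test uses p(1 − p)(1/n + 1/N). The reported z is therefore the correct z multiplied by r = √((1 − f)/(1 + f)), and the true size is 2·[1 − Φ(1.96/r)].

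| Reach f | r | 1.96/r | True size of nominal 5% test |
|---|---|---|---|
| 5% | 0.951 | 2.06 | 3.9% |
| 10% | 0.905 | 2.17 | 3.0% |
| 20% | 0.816 | 2.40 | 1.6% |
| 44% | 0.624 | 3.14 | 0.2% |

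The article gives no expected reach. The 44% is the acceptance rate cited in the Background from another ED study and serves only as an upper value. Simulation agrees with the table.

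**Power.** Inputs: 5,000 eligible (Effectiveness/reach section) and 40% women (assumed), so 2,000 women and 3,000 men. Worked case, with reach of 42% in women and 46% in men:

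- Enrolled: 840 + 1,380 = 2,220. Share of women: 37.84% of enrolled against 40% of eligible, a difference of 2.16 points.
- As written: pooled share (840 + 2,000)/7,220 = 0.393, so SE = √(0.393·0.607·(1/2,220 + 1/5,000)) = 0.01246 and the rejection threshold is 0.0244. The true SE is about √(0.24·(1/2,220 − 1/5,000)) = 0.00775. Power = Φ((0.0216 − 0.0244)/0.00775) ≈ 36%.
- Comparing reach directly: difference 0.04, null SE 0.01434, threshold 0.0281, SE under the alternative 0.0143. Power = Φ((0.04 − 0.0281)/0.0143) ≈ 80%.

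| Reach, women vs men | Power as written | Power, reach compared between groups |
|---|---|---|
| 5% vs 7% | 79% | 83% |
| 18% vs 21% | 59% | 74–75% |
| 42% vs 46% | 36% | 80% |

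**If the comparison were not stratified.** Assume 2,500 eligible per arm, reach of 20% (intervention) and 5% (control), and no disparity within any ED. There are 500 + 125 = 625 enrolled. With a racial group making up 40% of intervention and 20% of control patients, it forms (0.40·500 + 0.20·125)/625 = 36% of enrolled against 30% of eligible. SE = √(0.3067·0.6933·(1/625 + 1/5,000)) = 0.0196, z = 3.07, p = 0.002. With a mix of 35%/25%, z = 1.54, p = 0.12. With 33%/27%, z = 0.92, p = 0.36.

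Changing the contrast alone does not remove this. In a simulation with reach of 10% vs 20%, group shares of 30% and 50%, and no within-arm disparity, rejection was 40% for eligible against enrolled, 53% for enrolled against not enrolled without strata, and 4.7% with Mantel-Haenszel stratified by arm.

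**The case against.** The best defence has four parts.

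- **The harm may be small.** Patients must text a number themselves, and control sites get only an information session and flyers, so reach may be low. At 5% reach the true size is 3.9%, and the power loss at 5% vs 7% is about 4 points. This stands.
- **The error is conservative.** Overlap cannot produce a false claim of disparity. This stands too, but in a disparity check the missed gap is the costly error.
- **The Discussion already has the right contrast.** True, but both Methods sections state the other one, and the Analysis section is what an analyst would follow.
- **It is secondary.** The pilot's stated targets are feasibility, acceptability and reach, and the planned progression criteria rest on these. This stands and limits the weight of the point.

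A reader might infer more: that the plan pools the four EDs, and that the intended difference in reach between arms will by itself create false racial disparities. The document does not support that. It does not mention pooling, and a condensed article may leave stratification to a fuller plan. Unequal reach alone creates no false disparity: with equal mix in both arms, the simulated rejection rate stayed between 1.1% and 2.9%. Demographic mix must differ between EDs as well, and the article gives no figures on mix. The p = 0.002 above depends on an assumed two-fold difference in mix and vanishes under milder ones.

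**Conclusion.** The point holds for the overlap and for the inconsistency between sections. An independent-proportions z-test of the eligible against the enrolled uses the wrong variance, and the article describes two different contrasts for one analysis. The true size falls from 3.9% to 0.2% as reach goes from 5% to 44%. The power loss runs from about 4 points at the lowest reach examined to about 44 points at the highest. The size figures depend only on reach; the power figures also assume 40% women and the article's 5,000 eligible. Both take every enrollee to be an AUDIT-C-positive patient, as the reach measure itself does. The z-test for independent proportions is named for the arm comparison and is carried over here because the next sentence again specifies z-tests and names no other form. Confounding by ED is a conditional risk, not a demonstrated fault. The reach comparison and the 300 per condition are untouched.

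**What to change.** In the Aim 3 Effectiveness/reach and Analysis sections, replace the comparison of eligible with enrolled by enrolled against not enrolled, in line with the Discussion. Equivalently, compare reach between demographic groups, such as enrolled women over eligible women against enrolled men over eligible men. Stratify by ED, for example with a Mantel-Haenszel estimate and test, as a safeguard against differences in mix between sites. Not-enrolled counts are eligible minus enrolled for each ED and group. This requires demographic categories that can be matched between the EHR and the text platform.

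The cost is a change of wording. Enrollment by site code and demographics from both sources are already planned, so no new data or patients are needed.
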